On March 24, 2017, the use of nivolumab, an immune checkpoint inhibitor for patients with recurrent or metastatic head and neck cancer, was approved for insurance coverage in Japan. A few drugs are available to treat recurrent or metastatic head and neck cancers, and there are no established treatments for patients suffering from this condition; therefore, this drug is expected to serve as a new treatment option. The international Phase III trial (Checkmate-141 study) of nivolumab revealed significant OS prolongation in patients with platinum-resistant recurrent or metastatic head and neck cancer over the control arm of anticancer drugs and cetuximab. As mentioned above, FPE is the standard of care for recurrent and metastatic head and neck cancer. Still, it can further prolong survival and improve the quality of life for patients with poor prognosis. However, because the Checkmate 141 study included patients whose disease progressed within 6 months of completion of platinum-based chemotherapy, there is insufficient evidence in patients whose disease progressed after 6 months of completion of platinum-based chemotherapy.

2. Objectives

The purpose of this study is to evaluate the effects of nivolumab in patients with relapse or metastases 6 months after the completion of platinum-based chemotherapy.

3. Eligible patients

Expected number of patients: 50

(1) Inclusion criteria

Patients who met all the following criteria were included in this study:

1) Patients manifesting R/M-SCCHN six months after completing platinum-based chemotherapy

2) Primary site: the maxillary sinus, oral cavity, nasopharynx, oropharynx, hypopharynx, or larynx

3) Age 20-75 years

4) Eastern Cooperative Oncology Group performance-status (ECOG PS) score 0-1

5) Adequate organ functions defined as indicated below before registration in 14 days

(1) White Blood Cell ≧ 3,500 /mm3, White Blood Cell ≦ 12,000 /mm3

(2) neutrophil ≧ 2,000 /mm3

(3) Platelet ≧ 100,000 /mm3

(4) Hemoglobin ≧ 9.0 g/ dL

(5) Total bilirubin ≦ 1.5 mg/dL

(6) aspartate aminotransferase, alanine aminotransferase ≧ 100 IU/L

(7) Creatinine < 1.2 mg/dL

6) Written informed consent

(2) Exclusion criteria

Patients who met any of the following conditions were excluded from this study:

1) Patients with a history of severe drug allergy of nivolumab and similar drugs.

2) Patients with symptomatic brain metastasis and meningeal metastasis.

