3) Histologically proven primary unknown squamous cell carcinoma, salivary gland cancer, non-squamous cell cancer.

4) Patients with symptomatic autoimmune disease or history of autoimmune disease.

5) Patients with infection.

6) Patients with gastrointestinal disease (intestinal paralysis, bowel obstruction)

7) Patients with interstitial pneumonia or pulmonary fibrosis.

8) Uncontrolled diabetes.

9) Uncontrolled heart disorder.

10) Sever liver damage.

11) Patients with diarrhea.

12) Pregnant or lactating women or women with childbearing potential.

13) Men expecting partner's pregnancy.

14) Inadequate physical condition, as diagnosed by the attending physician

(3) Evidence for deciding the number of cases

This study is a single-arm phase II trial. The rate of recurrent or metastatic head and neck cancers at our institution is approximately 4 cases per month. Only 30% to 40% of the patients met the selection criteria and were eligible for enrollment. The study enrollment period is set at 2 years, and it is estimated that we will be able to enroll nearly 50 patients.

4. Material and Method

(1) Type and design

This is a prospective, interventional study in which nivolumab will be administered to subjects to evaluate treatment effects. It is an invasive study due to drug administration.

(2) Method

1) Patient enrollment

Patient enrollment will be determined by the principal investigator and sub-investigators.

2) Enrollment procedures

Confirm that eligible patients meet all eligibility criteria and none of the exclusion criteria, complete the Enrollment Eligibility Confirmation Form, and deliver it to the principal investigator. The principal investigator will review the information presented in the Enrollment Eligibility Confirmation Form and issue a registration number.

3) Treatment plan and treatment change criteria

Within 4 weeks of enrollment completion, treatment as per the protocol will be initiated under the direction of the principal investigator.

4) Protocol treatment

Nivolumab is administered at a single dose of 3 mg/kg (body weight) IV at 2-week intervals, which continues from the protocol initiation date until treatment is discontinued due to disease progression, unacceptable toxicity, other reasons.

5) Nivolumab discontinuation criteria

Discontinue nivolumab in the event of an adverse event (e.g., shock, anaphylactoid symptoms, etc.) determined to be attributable to this drug or in the event of a patient refusal.

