1) Hematological tests: hemoglobin, white blood cell count, neutrophil count, and platelet count

2) Blood biochemical tests: T.Bil, AST (GOT), ALT (GPT), Cr, Albumin, KL-6, SpO2, TSH, FT3, FT4, HbA1c, LDH*, ALP*, Na*, K*, Ca*, CRP*

Entries shall be made only for WBC, Neut, PLT, Hb, T.Bil, AST, ALT, Cr, KL-6, SPO2, TSH, FT3, FT4, HbA1c, and * shall be performed whenever possible

3) Ultrasound, CT, MRI, PET, histopathology, cytology, etc.

4) Tumor markers: SCC or CYFRA

5) PD-L1

6) Adverse events

Symptoms: fatigue (malaise), weight loss, skin rash/ desquamation, hyperpigmentation, loss of appetite, diarrhea, mucositis/stomatitis, nausea, vomiting, other (state as noted)

Grade: Indicates the highest grade for each case report period

Causation: yes, no

4) Lesion observation

Prior to the start of treatment and every 4 to 8 weeks of treatment, ultrasound, CT, MRI, and PET will be used to investigate the appearance of new lesions and other factors.

5) Health-related quality of life scores

The EORTC QLQ-C30 will be used as the baseline quality of life questionnaire used in malignant diseases, and the EORTC QLQ-H&N35 will be used as the disease-specific questionnaire. Quality of life questionnaires will be distributed to patients prior to the initiation of treatment and every 8 weeks after treatment initiation.

6) Subjective findings

Subjective symptoms and other findings should be monitored throughout the study period. Adverse events should be observed and examined as appropriate and, as a general rule, should be investigated until the event has resolved or the patient has returned to his or her pre-administration status, to the extent possible. This does not apply in the case of adverse events associated with the worsening of the primary disease.

The type and extent of adverse events should be in accordance with the NCI-CTC v4.0 JCOG version.

7) Follow-up items after termination (discontinuation)

Reason for termination (discontinuation), progress after discontinuation, and date of last observation

8) Time of data analysis

The survival of all patients will be investigated one year after enrollment of the last case after a total of 50 patients have been enrolled.

Once 20 patients have been enrolled, an interim evaluation and interim analysis will be conducted.

The interim analysis will also evaluate overall survival, progression-free survival, response rate, and health-related quality of life scores.

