In the event of discontinuation due to adverse events, patients will be monitored until symptoms and laboratory values return to their pre-trial status, if possible, or until the investigating physician determines that further observation is no longer necessary, considering the safety of the patient.

9) Schedule of examinations, observations, and reports

|  | At the time of registration | Under treatment | | | End of treatment |
| --- | --- | --- | --- | --- | --- |
| Each course  starting time | Each course  Day 8 | At the time of discontinuation of treatment |
| Background/Agreement | ● |  |  |  |  |
| PS | ● | ● | ● | ● | ● |
| Medication status |  | ● | ● | ● | ● |
| Clinical testing | ● | ● | ● | ● | ● |
| QOL score | ● | Every 8 weeks |  |  |  |
| Subjective symptoms | ● | ● | ● | ● | ● |
| Tumor markers | ○ | ○ | ○ | ○ | ○ |
| Image evaluation | ● | Every 4 to 8 weeks | | | |

●：Required ○：To be performed as needed

10) Data collection

recording paper

The types of Case Report Forms (CRFs) to be used in the examination and their submission deadlines are as follows:

1) Registration Eligibility Form

The principal investigator will be contacted at the time of registration. The principal investigator will issue a registration number after confirming the information on the registration eligibility form and drug dosage.

2) Case Report Form

To be submitted after discontinuation or termination of study treatment.

3) Follow-up report.

　The survival and post-treatment of all patients will be investigated one year after the last case enrollment.

5. Study period

The study period will be conducted from after the ethical review approval until December 31, 2021.

The enrollment period will be conducted until December 31, 2019.

The observation period will be from after the ethical review approval until December 31, 2020.

The data analysis period will include the period from January 1, 2020, and will be conducted until December 31, 2021.

Patients enrolled in this study will continue to receive treatment within the scope of insurance if therapeutic effects are observed after the end of the enrollment period.

Translated with www.DeepL.com/Translator (free version)

6. Informed consent

(1) Explaining to patients

Prior to enrollment, the study physician will give the patient a narrative document, approved by the Medical Ethics Committee, and will verbally explain in detail the following

1. Overview of the study

2. Purpose of the test

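### The protocol's own accrual figures give about 29 to 38 patients in two years, not the nearly 50 that is the only stated basis for the sample size

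*Protocol*

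**What the plan says.** Section 3 of the protocol gives the planned size as "Expected number of patients: 50". Section 3(3), which sets out the reasoning for that number, contains an accrual forecast and nothing else. It has three inputs and a conclusion:

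- Case load: "The rate of recurrent or metastatic head and neck cancers at our institution is approximately 4 cases per month".
- Eligible share: "Only 30% to 40% of the patients met the selection criteria and were eligible for enrollment".
- Period and conclusion: "The study enrollment period is set at 2 years, and it is estimated that we will be able to enroll nearly 50 patients".

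No target effect, error rate, power or precision is stated there.

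The figure of 50 returns in section 4(3), where item 8 fixes when the analyses are done: "The survival of all patients will be investigated one year after enrollment of the last case after a total of 50 patients have been enrolled". Item 10 of the same section (data collection, follow-up report) describes the survey again, one year after the last enrolment, without naming a number of patients. Section 5 (study period) sets calendar limits: "The enrollment period will be conducted until December 31, 2019" and "The observation period will be from after the ethical review approval until December 31, 2020".

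**The concern.** The conclusion of section 3(3) should be the product of its inputs, and it is not. Because the forecast is the only reason given for 50, the planned size has no support once the product fails.

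Two things follow. First, anyone judging what the study can show about overall survival, the primary endpoint, will assume 50 patients when the stated inputs point to roughly 60% to 75% of that. The expected number of participants is also one of the items to be explained to patients at consent (section 6(1)). Second, item 8 of section 4(3) describes the final survey as following the enrolment of 50 patients, a count that the stated inputs do not reach before enrolment closes. The protocol should say plainly what happens in that case.

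**Working it through.** **Inputs, all from the protocol.** About 4 cases a month, 30% to 40% eligible, and 24 months of enrolment (section 3(3)); planned number 50 (section 3); enrolment closing on 31 December 2019 (section 5); protocol dated 31 October 2017 (title page).

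**1. Attempt to reproduce the plan's figure.** Expected enrolment = cases per month × months × eligible share.

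- Cases in two years: 4 × 24 = 96.
- At 30% eligible: 96 × 0.30 = 28.8.
- At 40% eligible: 96 × 0.40 = 38.4.

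The stated inputs give about 29 to 38 patients, so nearly 50 is not reproduced. The shortfall is 50 − 38.4 = 11.6 to 50 − 28.8 = 21.2 patients, or 23% to 42% of 50. This assumes that every eligible patient consents.

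**2. More generous readings.**

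| Reading | 30% eligible | 40% eligible |
| --- | --- | --- |
| 4 a month, 24 months (as stated) | 28.8 | 38.4 |
| 4 a month, 26 months (protocol date to closing date) | 31.2 | 41.6 |
| 4.49 a month (the most that rounds to 4), 24 months | 32.3 | 43.1 |
| 4.49 a month, 26 months | 35.0 | 46.7 |

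The 26-month window is an upper bound, because section 5 starts the study only after ethics approval. Even with every input at its extreme, the result is below 47.

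**3. Chance variation.** If enrolment is Poisson with the means in step 1, the probability of at least 50 patients in 24 months is 0.02% at 30% eligible and 4.1% at 40%.

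**4. What 50 would require, changing one input at a time.**

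- Eligible share: 50 / 96 = 52%.
- Case rate: 50 / (24 × 0.40) = 5.2 to 50 / (24 × 0.30) = 6.9 a month.
- Duration: 50 / (4 × 0.40) = 31 to 50 / (4 × 0.30) = 42 months.

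**5. Illustration of precision.** The protocol gives no survival rate or precision target, so these figures rest on assumptions made here: a one-year overall survival rate of 50%, no censoring before one year, and the normal approximation to the binomial. The 95% half-width is 1.96 × √(0.25 / n).

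| n | Half-width (percentage points) |
| --- | --- |
| 50 | ±13.9 |
| 38 | ±15.9 |
| 29 | ±18.2 |

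**The case against.** Several points can be made for the protocol.

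- **It is a hedged forecast.** The wording is approximate throughout, and no hypothesis test or error rate depends on 50. That limits the harm. It does not make the product of the inputs come out near 50, even when each is stretched.
- **An input may be wrong rather than the total.** Section 5 carries a line showing that at least part of the English text was machine-translated, so the case rate or eligible share may be misreported and 50 may be what was meant. The document cannot settle this. The objection stands, and it decides the order of the fix.
- **Existing patients might add to the count.** The case rate appears to count new cases, and patients already under care at opening could in principle enrol. The protocol does not mention such a group, so the forecast cannot rest on it.
- **The final analysis does not hang on 50.** A reader might infer from item 8 of section 4(3) that the final survey would never fall due if fewer than 50 enrolled. The protocol does not support that reading. Item 10 of that section sets the survey one year after the last enrolment with no count condition, and section 5 ends enrolment and observation by date. What remains is a mismatch in wording between the two descriptions.
- **The interim is unaffected.** The protocol says "Once 20 patients have been enrolled, an interim evaluation and interim analysis will be conducted". A reader might object that 20 is 40% of 50 but 53% of 38 and 69% of 29. The protocol attaches no boundary or decision rule to that look, so the changed fraction alters nothing it states.
- **No power is lost against a stated target.** None is stated, so this is not a power error, and the half-widths in step 5 of the working are only illustrative.

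**Conclusion.** The point holds as an arithmetic inconsistency in the only stated basis for the sample size. Section 3(3) supports about 29 to 38 patients in two years, and at most 31 to 42 over the longest window that the dates allow at the stated case rate. Both ranges assume full consent. The gap to 50 is about 12 to 21 patients for the stated two years.

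The consequence is a planned size that the inputs do not support, with an illustrative loss of about 2 to 4 percentage points in the half-width for a one-year survival rate, under the assumptions given with that calculation. There is also a wording mismatch between items 8 and 10 of section 4(3) over when the final survey takes place. The documents do not support going further, to an analysis that might never be triggered, a compromised interim look or a failed power calculation.

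**What to change.** 1. Check the monthly case rate and the eligible share against the institution's records or the source-language text. If either is misreported, correct it so that the product agrees with the stated number.
2. If both are right, restate the expected number as about 29 to 38 for the two-year period in section 3, section 3(3) and item 8 of section 4(3).
3. State the precision of the survival estimate at the resulting size, together with the survival rate and censoring assumed.
4. Align items 8 and 10 of section 4(3) with section 5, so that the final survey and analysis take place one year after the last enrolled patient even if enrolment closes below 50.

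The cost is a protocol wording amendment, which section 6(3) makes subject to ethics committee approval. If the inputs prove right, the stated size and precision also become less favourable. No additional patients are needed.

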6) Withdrawal criteria and resumption criteria

At the initiation of nivolumab treatment (after the pre-course withdrawal period) or at any time during treatment, treatment should be continued after confirming that various laboratory tests have met the dosage criteria. If the dosage criteria are not met, the drug should be withdrawn and resumed according to the following criteria.

7) Criteria for drug withdrawal

If any of the following withdrawal criteria are met during treatment, treatment should be discontinued immediately, and treatment should be resumed while waiting for the patient's recovery to reach or exceed the withdrawal criteria.

In cases where the baseline is close to the withdrawal criteria, the investigator/assigned physician will decide on whether to discontinue treatment at the time the withdrawal criteria are violated.

| Inspection item | | Criteria for drug withdrawal | |
| --- | --- | --- | --- |
| Criteria for drug withdrawalBlood toxicity | White blood cell | < | 3,000 /mm3 |
| Neutrophil | < | 1,500 /mm3 |
| Platelet | < | 100,000 /mm3 |
| Hemoglobin | < | 9.0 g/ dL |
| Non-blood toxicity | Total bilirubin | ≧ | 2.0 mg/dL |
| Aspartate aminotransferase | ≧ | 100 IU/L |
| Alanine aminotransferase | ≧ | 100 IU/L |
| Creatinine | ≧ | 1.2 mg/dL |
| Other adverse events | ≧ | Grade2 |

8) Criteria for resuming administration

In the case of nivolumab administration, the following "Resumption Criteria" should be met before initiating nivolumab administration. The dose at the resumption of nivolumab administration is determined after confirming that the dose reduction criteria have been met.

If the withdrawal period for adverse events exceeds 28 days, the treatment is discontinued in this patient.

| Inspection item | | Criteria for resuming administration | |
| --- | --- | --- | --- |
| Blood toxicity | White blood cells | ≧ | 3,000 /mm3 |
| Neutrophil | ≧ | 1,500 /mm3 |
| Platelet | ≧ | 100,000 /mm3 |
| Hemoglobin | ≧ | 9.0 g/ dL |
| Non-blood toxicity | Total bilirubin | < | 2.0 mg/dL |
| Aspartate aminotransferase | < | 100 IU/L |
| Alanine aminotransferase | < | 100 IU/L |
| Creatinine | < | 1.2 mg/dL |
| Other adverse events | < | Grade1 |

9) Drug information

The following is a summary of the drug used in this study. Please refer to the most recent package insert for the drug for further information.

Nivolumab:

Generic name: Nivolumab

Product Name: Opdivo

[Contraindication]

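### Protocol section 4(2) gives two different restart conditions for nivolumab after a non-laboratory adverse event, and does not separate a pause from a permanent stop

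*Protocol*

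**What the plan says.** All of the rules are in section 4(2) of the protocol.

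- **4), protocol treatment:** "Nivolumab is administered at a single dose of 3 mg/kg (body weight) IV at 2-week intervals", continuing "until treatment is discontinued due to disease progression, unacceptable toxicity, other reasons". No second dose level is given.
- **5), discontinuation:** "Discontinue nivolumab in the event of an adverse event (e.g., shock, anaphylactoid symptoms, etc.) determined to be attributable to this drug", or if the patient refuses. No grade is attached.
- **7), withdrawal:** the last non-laboratory row of the table reads "Other adverse events | ≧ | Grade2". The text above the table says that once a criterion is met treatment stops at once, and then that "treatment should be resumed while waiting for the patient's recovery to reach or exceed the withdrawal criteria".
- **8), resumption:** the resumption criteria have to be satisfied before nivolumab is given. The matching row reads "Other adverse events | < | Grade1". The section adds "The dose at the resumption of nivolumab administration is determined after confirming that the dose reduction criteria have been met" and "If the withdrawal period for adverse events exceeds 28 days, the treatment is discontinued in this patient".

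**The concern.** A physician with a paused patient needs three answers from this section: whether the event calls for a pause or a permanent stop, when treatment may restart, and at what dose. On the first two, different sentences give different answers. On the third, the text refers to criteria that are not there.

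The 28-day limit makes the second question matter. If the restart condition is unclear, so is whether a patient with lingering low-grade toxicity returns to treatment or is taken off it permanently. That is a safety matter for the patient. In a single-arm study it also means that drug exposure and time on treatment depend partly on which sentence was followed. Monitoring under section 21 covers protocol deviations and reasons for stopping, and a deviation cannot be judged against two conflicting rules.

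**Working it through.** No sample-size or error-rate figure enters this point, so the check is a comparison of the rules.

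**Step 1. Laboratory rows.** The pause limit in 7) is set against the restart limit in 8):

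| Item | Pause (7) | Restart (8) |
| --- | --- | --- |
| White cells, /mm3 | < 3,000 | ≥ 3,000 |
| Neutrophils, /mm3 | < 1,500 | ≥ 1,500 |
| Platelets, /mm3 | < 100,000 | ≥ 100,000 |
| Hemoglobin, g/dL | < 9.0 | ≥ 9.0 |
| Total bilirubin, mg/dL | ≥ 2.0 | < 2.0 |
| AST, IU/L | ≥ 100 | < 100 |
| ALT, IU/L | ≥ 100 | < 100 |
| Creatinine, mg/dL | ≥ 1.2 | < 1.2 |

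All eight pairs are exact complements. Recovering past the pause limit and meeting the restart limit are the same condition, so these limits do not conflict.

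**Step 2. Other adverse events, after a pause.** The pause limit is Grade 2 or higher and the restart limit is below Grade 1, so the two conditions differ:

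| Grade now | Text of 7) | Section 8) |
| --- | --- | --- |
| 0 | restart | restart |
| 1 | restart (no longer in the pause range) | no restart |
| 2 or higher | read literally, restart while recovery is awaited; read for sense, still paused | no restart |

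Grade 1 is a conflict on either reading of 7). Grade 2 or higher is a conflict only on the literal reading.

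**Step 3. The 28-day rule.** Twenty-eight days is two dosing intervals (2 × 14). Take an event that falls from Grade 2 to Grade 1 and stays there. Under the text of 7), treatment can resume when the event leaves Grade 2, and the pause ends. Under 8), the pause continues, and after day 28 treatment ends permanently.

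**Step 4. Section 5) against 7) and 8).**

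| Event | Section 5) as worded | Sections 7) and 8) |
| --- | --- | --- |
| Drug-attributed, Grade 1 | stop | no pause |
| Drug-attributed, Grade 2 or higher | stop | pause, restart possible |
| Not attributed, Grade 2 or higher | not covered | pause, restart possible |

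Section 15(2) counts laboratory abnormalities as adverse events, so a drug-attributed laboratory abnormality that meets a pause limit also falls under both rules.

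**Step 5. Terms.** *Discontinue* means a permanent end of treatment in 4), 5) and the 28-day sentence of 8). In 7) the same verb describes an interruption that is followed by a restart.

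**Step 6. Restart dose.** Section 8) makes the restart dose depend on dose-reduction criteria. None appear in the document shown, and 4) gives a single level.

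**Step 7. Size.** The number of patients affected would require the share paused for a non-laboratory event and the share of those still at Grade 1 after 28 days. The protocol gives neither, so no figure is offered.

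**The case against.** The best defence is that 7) governs pausing and 8) governs restarting. Section 6) points forward to the criteria that follow, 8) carries the resumption heading, and the sentence in 7) is awkward enough to be a translation fault; section 5 of the protocol carries a machine-translation notice. On that view the table in 8) simply prevails. This is a plausible account of what was meant, but the text does not say that 8) overrides 7), and a physician who follows 7) as worded reaches a different decision.

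Several parts of the defence stand, and they rule out stronger readings that a reader might infer:

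- **That the gap between Grade 2 and below Grade 1 is itself an error.** It is not. A restart limit stricter than the pause limit is a legitimate choice. The conflict arises only because 7) names a different restart point.
- **That a Grade 1 symptom bars the first dose.** Section 8) does speak of initiating administration, but its heading and next sentence concern resumption. Section 6) refers only to laboratory tests at initiation, and section 15(2) defines adverse events in subjects who receive the drug.
- **That 5) flatly contradicts 7) and 8).** Its examples, shock and anaphylactoid symptoms, suggest severe reactions. What remains is an overlap with no stated boundary.
- **That two restart doses are prescribed.** They are not. The dose-reduction item is a reference with nothing behind it.
- **That overall or progression-free survival is directly distorted.** The definition of overall survival does not change, and survival is to be investigated in all patients one year after the last enrolment (section 4(3)8)). Any effect through exposure is indirect and unquantified.

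Section 15(2) also treats an adverse event as a worsening of at least one grade. A return to a Grade 1 baseline is then arguably no longer an event, which narrows the affected group. This is a single-centre study with treatment started under the principal investigator's direction, which limits divergent readings but does not remove them.

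**Conclusion.** The inconsistency is real and should be fixed. For non-laboratory adverse events, 7) and 8) give different restart conditions, and with the 28-day rule an event that settles at Grade 1 may lead to restart on one reading and permanent stopping on the other. The scope of 5), the double use of *discontinue* and the missing dose-reduction criteria add to the uncertainty but are lesser points.

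The consequences are for patient safety, drug exposure and the judging of deviations. Their size cannot be computed from the documents.

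The conclusion takes the protocol text as written to be what staff follow. If a source-language version is clear, the fault may lie in the translation alone. A portion after the monitoring section was not available; it is unlikely to hold dosing criteria, though this cannot be excluded. Nothing here says which grade, dose or stopping rule is right.

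**What to change.** Reconcile sections 4(2)5), 7) and 8), with the clinical team setting the content:

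1. State one restart condition for other adverse events, identical in the text of 7) and the table in 8).
2. Define which events fall under 5) so that it no longer overlaps the pause rule, and use separate terms for a pause and a permanent stop.
3. Either insert the dose-reduction criteria that 8) cites or delete the reference.
4. Record on the case report form which rule triggered each pause as well as each stop. The reason for ending treatment is already collected (section 4(3)7)) and monitored (section 21), so the reason for a pause and the rule applied are the additions.

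The cost is an amendment to one section, with the principal investigator and ethics committee approval that section 6(3)2) requires, and a small change to the case report form. No new study procedure is needed.

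### The baseline QoL form is scheduled at registration, but follow-up forms run from treatment start up to 4 weeks later, so QoL change can include untreated weeks

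*Protocol*

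**What the plan says.** Three places in the protocol together set the timing of QoL measurement.

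- **Section 4(3)9), schedule of examinations.** The first column is headed "At the time of registration". The QoL row reads "QOL score | ● | Every 8 weeks": one required mark at registration, then the repeat interval. It shows no separate mark for a form at the start of the first course.
- **Section 4(3)5), health-related quality of life.** Forms are given out "prior to the initiation of treatment and every 8 weeks after treatment initiation". This sets the follow-up clock at treatment start, but fixes the baseline only as some time before it.
- **Section 4(2)3), treatment plan.** "Within 4 weeks of enrollment completion, treatment as per the protocol will be initiated". The permitted wait is thus 0 to 4 weeks.

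No maximum interval between the baseline form and the first dose is stated. Other items are tied down more closely. Organ function has a window in section 3(1), item 5: "Adequate organ functions defined as indicated below before registration in 14 days". Section 4(2)6) has laboratory values checked at the start of treatment. The schedule repeats performance status, clinical testing and subjective symptoms at each course start.

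**The concern.** Baseline and follow-up run on two clocks. If the baseline form is completed at registration and the patient waits for the first infusion, the form labelled week 8 measures change over the wait plus 8 weeks of treatment. Patients with recurrent or metastatic disease may get worse during the wait, and that worsening would then be part of the change attributed to nivolumab.

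The single-arm design makes this matter. A concurrent control arm would share the waiting-time drift and largely cancel it. Here each patient's own baseline is the only comparator for QoL change. Section 8(1) anticipates that nivolumab may improve QoL, and a baseline taken before an untreated decline works against seeing such an improvement. The wait can also differ between patients, so the same nominal week can stand for different lengths of time since baseline. Analysis cannot supply a pre-dose form that was never collected.

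**Working it through.** The protocol gives no figure of its own to reproduce here, so the check is of visit timing.

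**Inputs**
- Gap *g* from the registration form to the first dose: 0 to 4 weeks (section 4(2)3), with the baseline at registration as in section 4(3)9)).
- Nominal follow-up week *w*, counted from treatment start: 8 and 16 (8-week interval in section 4(3)5); both time points appear in Supplementary Table 1).

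**Formula**
Untreated share of the interval from baseline to assessment = *g* / (*g* + *w*).

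| Gap *g* (weeks) | Week 8 | Week 16 |
| --- | --- | --- |
| 0 | 0/8 = 0% | 0/16 = 0% |
| 1 | 1/9 = 11% | 1/17 = 6% |
| 2 | 2/10 = 20% | 2/18 = 11% |
| 4 | 4/12 = 33% | 4/20 = 20% |

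These are shares of elapsed time, not of score change. If the form is completed just before the first infusion, *g* = 0 and the share is zero at every visit.

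**Illustration in score points.** The documents give neither actual gaps nor a rate of untreated decline. Assume, for scale only, that every patient waited the full 4 weeks after a registration form and that change is linear over time. Applied to physical functioning in Supplementary Table 1:
- Week 8: reported change −0.7, of which 0.7 × 4/12 = 0.2 points would fall before treatment. The 95% CI (−5.9 to 4.5) has half-width (4.5 + 5.9)/2 = 5.2.
- Week 16: reported change −4.1, of which 4.1 × 4/20 = 0.8 points would fall before treatment. The 95% CI (−10.0 to 1.8) has half-width (1.8 + 10.0)/2 = 5.9.

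Under these assumptions the pre-treatment part is small beside the sampling error. A faster decline before treatment than on it would make that part larger.

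**The case against.** The strongest reply is that the baseline is not fixed at registration at all. Section 4(3)5) is the section specific to QoL, and it allows a form just before the first dose. The sentence in section 4(3)3) that sends timing to the schedule sits under the test items, where QoL is not listed, and it cites a schedule number (8.2) that this protocol does not use. The schedule table has also lost header cells in extraction, so the lack of a separate first-course mark is weak evidence that no such form was intended. Supplementary Table 1 labels its baseline only as pre-nivolumab, which fits either reading.

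This stands to the extent that one cannot say the baseline was necessarily taken at registration, or that untreated change was in fact counted. It does not remove the point. The registration column is marked as required, no form is expressly required at first dose, and the looser wording sets no limit on the interval. Either reading leaves the timing open and calls for the same repair.

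It is also fair that QoL is a secondary endpoint, and that deterioration during the wait would count against the drug, so it would not create a false claim of benefit. That limits the weight of the point. It could still hide an improvement or make QoL appear to worsen on treatment.

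A reader might extend the argument to imaging, since that row has the same form ("Image evaluation | ● | Every 4 to 8 weeks") and section 4(3)4) likewise places the first assessment before treatment. The documents do not support a claim that response or progression is distorted:
- A scan at registration followed by a start within 4 weeks already lies within 28 days of first dose, so a 28-day rule would change nothing.
- The protocol gives no tumour growth rate and no numerical progression threshold.
- That the scan which first showed the relapse could serve as baseline is conjecture, given the required mark at registration.
- The time origin of progression-free survival is not stated, so no direction of bias follows for it.

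**Conclusion.** The point holds for QoL change, as a looseness in timing that can introduce bias. The change from baseline at week 8 can include 0 to 4 untreated weeks, at most 33% of elapsed time, and at week 16 at most 20%. The upper figures assume a registration form and the full permitted wait. With a form just before the first dose, or treatment started at once, the share is zero.

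How many score points this represents cannot be determined from the protocol. A reader might infer that a third of the reported week-8 change is untreated decline. The documents do not show that: the fraction is of calendar time, and 4 weeks is a ceiling. Overall survival, the primary endpoint, does not depend on the QoL baseline. The defect is worth correcting because the correction is nearly free, but it does not threaten the main result.

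**What to change.** Make sections 4(3)5) and 4(3)9) agree. In the schedule, place the baseline QLQ-C30 and QLQ-H&N35 at the first-course visit, to be completed before the first infusion. Use the same wording in section 4(3)5), and state that QoL change is measured from that form. Baseline and follow-up then share one clock and the untreated share is zero by design.

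The cost is a change of wording in two places, since the patient is already on site for the infusion. The one downside is that patients who register but never start treatment would have no baseline form. If they are to be described, keep the registration form as well, as a descriptive record and not as the reference for change.
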